## Abstract

**Background:**

Malnutrition is a common consequence of disease in older patients. Both in hospital setting and in community setting oral nutritional support has proven to be effective. However, cost-effectiveness studies are scarce. Therefore, the aim of our study is to investigate the effectiveness and cost-effectiveness of transmural nutritional support in malnourished elderly patients, starting at hospital admission until three months after discharge.

**Methods:**

This study is a randomized controlled trial. Patients are included at hospital admission and followed until three months after discharge. Patients are eligible to be included when they are ≥ 60 years old and malnourished according to the following objective standards: Body Mass Index (BMI in kg/m^2^) < 20 and/or ≥ 5% unintentional weight loss in the previous month and/or ≥ 10% unintentional weight loss in the previous six months. We will compare usual nutritional care with transmural nutritional support (energy and protein enriched diet, two additional servings of an oral nutritional supplement, vitamin D and calcium supplementation, and consultations by a dietitian). Each study arm will consist of 100 patients. The primary outcome parameters will be changes in activities of daily living (determined as functional limitations and physical activity) between intervention and control group. Secondary outcomes will be changes in body weight, body composition, quality of life, and muscle strength. An economic evaluation from a societal perspective will be conducted alongside the randomised trial to evaluate the cost-effectiveness of the intervention in comparison with usual care.

**Conclusion:**

In this randomized controlled trial we will evaluate the effect of transmural nutritional support in malnourished elderly patients after hospital discharge, compared to usual care. Primary endpoints of the study are changes in activities of daily living, body weight, body composition, quality of life, and muscle strength. An economic evaluation will be performed to evaluate the cost-effectiveness of the intervention in comparison with usual care.

**Trial registration:**

Netherlands Trial Register (ISRCTN29617677, registered 14-Sep-2005)

## Background

The primary cause of malnutrition in developed countries is disease. Malnutrition is estimated to occur in 25-61% of all elderly patients suffering from a variety of diseases [1,2]. Unintentional weight loss of ≥ 5% in the previous month and/or unintentional weight loss of ≥ 10% in the previous six months and/or a BMI <20 kg/m^2 ^are often used as parameters to identify malnutrition.

Disease related malnutrition is associated with adverse effects on clinical outcome, as has been shown in a large number of studies. These adverse effects vary from impaired wound healing and postoperative complications to mortality [3]. Poor nutritional status has not only been associated with in-hospital adverse effects, but also with adverse effects both pre-admission and post-discharge. These effects include a trend for increased need for re-hospitalization, significantly higher total mortality, a higher general practitioner consultation rate, higher medication prescription rate, longer rehabilitation, an increased need for nursing home admission, increased likelihood of requiring home health care after discharge and early institutionalization [4,5].

So far, randomized clinical trials have shown that additional Oral Nutritional Support (ONS) can be effective in malnourished elderly people, both in the clinical setting and in the community [6]. In hospitalized patients ONS has been shown to reduce weight loss, to shorten hospital stay and to improve functional status in malnourished hospitalized patients. In the community ONS has been shown to increase activities of daily living, to reduce the number of falls and to reduce health care utilization [5,7-10].

Furthermore, a meta-analysis, including 31 studies and almost 2500 patients, showed that protein and energy supplementation led to small changes in weight and, more importantly to reduced mortality (RR 0,67; CI 0,52-0,87). Also, length of hospital stay was reduced by on average 3.3 days (CI -9.64-3.05) [7].

Because nowadays patients spend only a minority of time in hospital and recover at home, it is not very likely that patients' nutritional status will improve during the short period of admission. Therefore, the problem of disease related malnutrition is more and more becoming a post-discharge problem (in this manuscript further referred to as a transmural problem).

For in-hospital patients, studies on cost-effectiveness of nutritional interventions are scarce. In a retrospective cost-analysis of nine randomized controlled trials on nutritional support, the cost savings aggregated between €503 and €11696 per patient in surgical, orthopedic, elderly and stroke patients [6]. A recent observational cohort study showed a cost reduction in patients supplied with ONS of €723 per patient [8]. In a prospective study, a reduction of length of hospital stay with one day was achieved with an investment of €34 per malnourished patient [11].

Cost-effectiveness studies of ONS in the community are lacking and are eagerly awaited for. We do expect that a nutritional intervention in the transmural setting will be accompanied by higher health care costs than usual care, but that these higher costs are negligible compared with the cost-savings they can potentially generate.

The aim of this study is to investigate the cost-effectiveness of transmural nutritional support in malnourished elderly patients after hospital discharge as compared to usual care on changes in activities of daily living. Secondary outcomes include changes in body weight, body composition, quality of life, and muscle strength between intervention and control group.

## Methods

### Design

This study is designed as a randomized controlled trial comparing transmural nutritional support with usual nutritional care. The study design is in accordance with the Declaration of Helsinki and has been approved by the Medical Ethics Committee (METC) of VU University Medical Center.

Patients are eligible for this study when they are ≥ 60 years old and malnourished according to the following objective standards: Body Mass Index (BMI in kg/m^2^) < 20 and/or, ≥ 5% unintentional weight loss in the previous month and/or ≥ 10% unintentional weight loss in the previous six months. We will compare usual nutritional care with transmural nutritional support (energy and protein enriched diet, two additional servings of an oral nutritional supplement, vitamin D and calcium supplementation, and consultations by a dietitian). The primary outcome parameters will be changes in activities of daily living (functional limitations and physical activity) between the intervention and control group. Secondary outcomes will be changes in body weight, body composition, quality of life, and muscle strength. An economic evaluation from a societal perspective will be conducted alongside the randomised trial to evaluate the cost-effectiveness of the intervention versus usual care.

### Feasibility of recruitment and sample size

Earlier studies have shown that 30% of the elderly hospital population is malnourished at admission [12-16]. For a clinically relevant difference of 20% in nutritional and functional status with a statistical significance level of 0.05 and a power of 80%, two groups of 80 patients were calculated to be sufficient.

A pilot study showed that inclusion of 140 malnourished patients per year is feasible. Taking into account an expected refusal rate of 30% at inclusion and loss to follow-up of 10% during the three months following discharge, we aim to include two groups of 100, to be reached in approximately two years.

### Population, inclusion and exclusion criteria

All elderly patients (≥ 60 years of age, expected length of hospital admission >2 days) newly admitted to the wards of internal medicine, traumatology and vascular surgery of the VU University Medical Center will be screened at admission by a dietitian and/or research assistants of nutritional status. These departments represent the (sub)specialties general internal medicine, rheumatology, gastroenterology, dermatology, nephrology, orthopedics, traumatology and vascular surgery.

Patients will be excluded from the study when they suffer from senile dementia, can not understand the Dutch language or are not able to or willing to give informed consent.

### Nutritional status

Patients are be eligible for this study if they are identified malnourished according to the following criteria:

• Body Mass Index (BMI in kg/m^2^) < 20 and/or

• ≥ 5% unintentional weight loss in the previous month and/or

• ≥ 10% unintentional weight loss in the previous six months.

Weight (in kg to the nearest decimal) is measured (with patients wearing light indoor clothes and no shoes) on a calibrated chair scale (Prior MD-1512), with an accuracy of 0.1 kilogram, at admission and three months after discharge. A correction factor for clothes will be made by deducting weight with 2.0 kilograms for men and 1.3 kilograms for women [17].

BMI is calculated as actual weight in kilograms divided by the square of height in meters.

As measurement of height is often not feasible in this ill, old and frail population, data on height will be retrieved from self-reported height, with an accuracy of 1.0 centimeter. These data will be validated against height derived from knee height measurements (Seca 207, in cm to the nearest decimal) in approximately 800 elderly patients from the same departments at our institute.

### Intervention

Control patients will receive 'usual' nutritional care, i.e. hospital intervention only on referral by the treating physician and without standardized transmural nutritional support.

Patients assigned to the intervention group strategy will receive standardized transmural nutritional support (**Appendix 1**) starting in hospital and to be continued until three months after discharge.

### Procedure

After obtaining patients' informed consent an inventory will be made of nutritional status, nutritional risk profile and possible confounders. This includes the following baseline characteristics:

- sociodemographic data (age, gender, education level, partner status)

- medical history and medical diagnosis

- anthropometry (weight, height, BMI, percentage involuntary weight loss)

- biochemical parameters (CRP, IGF-1, 25(OH)D)

- mental state (MMSE) [18]

- expected care complexity (COMPRI) [19]

Information on disease, disease severity, disease course, treatment and complications will be retrieved from medical records.

Post-discharge practice will be followed and outcome parameters will be collected for all patients at three months after discharge.

### Outcome parameters

Outcome parameters will be measured after inclusion and at three months after discharge.

Primary outcome is change in activities of daily living, determined as functional limitations and physical activities. All outcome parameters that will be measured are listed below.

#### Activities of daily living

Activities of daily living (ADL) will be assessed with a validated questionnaire that measures the degree of difficulties patients experience with six activities: climbing stairs, walking 5 minutes outdoors without resting, getting up and sitting down in a chair, dressing and undressing oneself, using own or public transportation, and cutting one's own toenails [20]. Functional limitations will be assessed using five difficulty categories, ranging from "No I can not' to 'Yes without difficulty'. Total score will be calculated by summing the scores of all activities, ranging from 0 (does not have any difficulties with the activities) to 6 (has difficulties with all activities).

#### Physical performance

The performance test of physical function includes time measures of walking speed, rising from a chair, putting on and taking off a cardigan, and maintaining balance in a tandem stand [21-23]. To test walking performance a 3 meter walking course is created by a measuring line. Patients are instructed to walk to the other end of the course, to turn 180 degrees, and walk back as quickly as possible. Patients are allowed to use a walking aid if necessary. To test the ability to rise from a chair, patients are asked to fold their arms across their chest and to stand up and sit down five times from a standard hospital chair as quickly as possible. For the cardigan test, patients are asked to put on and take off a cardigan as quickly as possible. To test for balance, patients are asked to stand with one foot placed behind the other in a straight line for at least 10 seconds.

A trained research assistant records the total time needed to complete each test.

Patients who complete the walking test, chair test and cardigan test will be assigned scores between 1 and 4, corresponding to the quartiles of time needed to complete the test, with the fastest time scored as 4. Those who cannot complete the test will be assigned a score of 0. Accordingly the maximum score for these three tests ranges from 0-12 points, after adding up the result of these tree tests.

The balance test will be analyzed separately, yet with the same time classification as described above.

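### The tandem-stand balance test is given a speed-test scoring rule that, read literally, inverts or ties the scores of the patients it classifies

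*Protocol article*

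**What the plan says.** All of this is in the protocol article, Methods, Physical performance.

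- **Speed tests.** Walking, five chair rises and the cardigan test are each done as fast as the patient can. Completers score 1 to 4, "corresponding to the quartiles of time needed to complete the test, with the fastest time scored as 4".
- **Unable.** "Those who cannot complete the test will be assigned a score of 0".
- **Recording.** "A trained research assistant records the total time needed to complete each test".
- **Balance task.** For the tandem stand, "patients are asked to stand with one foot placed behind the other in a straight line for at least 10 seconds".
- **Balance scoring.** "The balance test will be analyzed separately, yet with the same time classification as described above".

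The three speed tests are summed to a score of 0 to 12; balance is kept out of that sum. Outcome parameters states that outcomes are measured after inclusion and three months after discharge. Physical performance is among the outcomes described, but Design and Outcome parameters do not name it as primary, and Design does not list it as secondary.

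**The concern.** The scoring direction suits tasks in which a short time shows good function. In a tandem stand a short time shows poor balance. Carrying the rule over without a stated reversal means that a programmer who follows the text would give better scores to worse balance among the patients whose hold times are classified. Recording the time needed to complete a test also has no clear meaning for a hold: if the stopwatch stops at the 10-second target, every completer has the same time and no quartiles can be formed.

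At stake is a separately analysed balance outcome. Its score could point the wrong way for some patients, or carry no more information than pass or fail while being presented as a graded scale.

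**Working it through.** **Inputs** (all from Physical performance): quartile scores 1 to 4 with the shortest time scored 4; 0 for unable; a tandem-stand target of at least 10 s; the same classification applied to balance.

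**The plan's own figure.** Three tests, each scored 0 to 4: 3 × 0 = 0 and 3 × 4 = 12. The stated range of 0-12 reproduces with balance left out, so the balance rule cannot alter that score.

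**The balance rule under three literal readings.**

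*Reading A: every hold time is ranked.* Take eight illustrative holds (assumed; the article gives no data): 1, 3, 5, 7, 9, 10, 10, 10 s. Quartiles by linear interpolation, counting positions from 0:
- 25%: position 0.25 × 7 = 1.75, giving 3 + 0.75 × (5 − 3) = 4.5 s
- 50%: position 0.50 × 7 = 3.5, giving 7 + 0.5 × (9 − 7) = 8 s
- 75%: position 0.75 × 7 = 5.25, giving 10 s

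With the shortest scored 4: up to 4.5 s scores 4; above 4.5 to 8 s scores 3; above 8 to 10 s scores 2.

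| Hold (s) | 1 | 3 | 5 | 7 | 9 | 10 | 10 | 10 |
|---|---|---|---|---|---|---|---|---|
| Score | 4 | 4 | 3 | 3 | 2 | 2 | 2 | 2 |

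The order is inverted: the patient who loses balance after 1 s outscores the three who reach the target.

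*Reading B: under 10 s is unable (0), and timing stops at 10 s.* Every completer has a time of 10 s, so all three quartile cut-offs equal 10 s and all completers share one score. The result is a pass/fail outcome on a scale labelled 0 to 4. Failures rank lowest, which is the right direction.

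*Reading C: under 10 s is unable (0), and timing continues beyond 10 s.* Failures score 0, the longest-holding quarter of completers scores 1, and the shortest-holding quarter scores 4. A patient who moves from failing to holding gains between 1 − 0 = 1 and 4 − 0 = 4 points. A completer who moves from the shortest to the longest quarter changes by 1 − 4 = −3 points while improving.

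None of the three readings gives a graded score that rises with balance.

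**Side check: quartile cut-offs for the speed tests.** The article does not say which times supply the quartiles. A simulation compared cut-offs re-derived at each visit with cut-offs fixed at pooled baseline. Assumed inputs: 2,000 runs, 90 completers per arm, log-normal times with log-SD 0.4, correlation 0.7 between visits, and no zeros. Results are mean change per test; between-arm differences were taken before rounding.

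| Gain in speed (intervention / control) | Per-visit cut-offs | Between-arm | Baseline cut-offs | Between-arm |
|---|---|---|---|---|
| 20% / 20% | 0.00 / 0.00 | about 0 | +0.56 / +0.56 | about 0 |
| 30% / 10% | +0.32 / −0.32 | 0.63 | +0.84 / +0.27 | 0.57 |
| 20% / 0% | +0.28 / −0.28 | 0.56 | +0.56 / 0.00 | 0.55 |

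Per-visit cut-offs distort within-arm change but largely keep the randomised contrast.

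**The case against.** The strongest reply is that the wording is loose and the analysis itself may be sound. The phrase about the same classification may mean only the grouping into 0 and four quartile scores, with direction adapted to a hold. The article is condensed and cites sources for these tests that are not at hand. This lowers the likelihood that a reversed analysis would actually be run. It does not rescue the text, which states a direction, "with the fastest time scored as 4", and no exception for balance. Even with the direction reversed, stopping the watch at 10 s leaves all completers tied.

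Two stronger readings may tempt a reader, and the article supports neither.

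- **That the balance score is wholly reversed, so benefit would appear as harm.** The task is to "stand with one foot placed behind the other in a straight line for at least 10 seconds", and inability scores 0. On the natural reading a shorter hold is non-completion and ranks below every completer, so recovering the ability to hold raises the score. Full inversion needs holds under 10 s to be ranked as completed tests, which the text does not say.
- **That change in physical performance is not measured because the quartiles shift between visits.** The text never says that cut-offs are recomputed. The reference distribution is a detail an article may leave to the full protocol or analysis plan. Even with recomputed cut-offs the between-arm difference is largely kept, as the table shows, and patients moving from unable to able would still raise the mean score.

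It is also fair to say that the stakes are limited: balance lies outside the 0-12 score, and physical performance is not a named primary or secondary outcome.

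**Conclusion.** The point holds for the balance test only. The article states a scoring rule that does not fit a hold test: read literally, it inverts the order among patients whose holds are ranked, or ties all completers if timing stops at 10 s. Patients scored as unable still rank lowest under Readings B and C, so the error is then confined to completers; it reaches the whole scale only under Reading A. How many patients are affected cannot be stated, because the article gives no distribution of hold times.

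The inversion and the ties follow from the wording alone; the eight hold times only illustrate them. The 0-12 score is not affected, and no named primary or secondary outcome is shown to depend on the rule. The cut-offs for the speed tests are a matter for clarification and are not an error.

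**What to change.** Replace the balance sentence with one of the following:

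- score the tandem stand as held for 10 s or not, and analyse it by logistic regression, which Statistical analyses already specifies for dichotomous outcomes; or
- score it by hold time with a longer hold scoring higher and unable as 0, stating whether timing stops at 10 s and how a hold under 10 s is scored.

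The first option is simpler and avoids the problem of ties.

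As an optional clarification, state that the quartile cut-offs for walking, chair rise and cardigan are derived once, for example from baseline times pooled over both arms, and applied at both visits. Within-arm change can then be interpreted as well as the between-arm difference.

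The cost is a sentence or two and the scoring code. Pass/fail scoring needs no new measurement.

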#### Physical activity

Physical activity will be assessed with the validated LASA Physical Activity Questionnaire (LAPAQ) [24]. This face-to-face questionnaire covers the frequency and duration of walking outside, cycling, gardening, sports and household activities during the previous two weeks. Walking and bicycling for transportation purposes are considered as common daily activities in The Netherlands, and not as sports activities. For the analyses, the total time spent on physical activity of the last two weeks is used (in minutes per day).

#### Quality of life

Quality of Life will be measured by the SF-12 and EuroQol (EQ-5D and EQ-VAS).

The SF-12 contains 12 questions from the SF-36 [25]. These questions concern functional status -both physical and social functioning-mental health, pain, vitality and evaluation of persons' state of health. With these dimensions two total scores can be calculated; one physical component score and one mental component score [26].

EuroQol (EQ-5D) is a standardised instrument to monitor health outcome [27]. This instrument contains five short questions on mobility, self-care, daily activities, pain/discomfort and anxiety/depression with three possible response categories (no problems, moderate problems, severe problems). The EQ-5D scores were used to calculate utilities using the Dutch tariff [28]. QALYs were calculated by multiplying the utilities with the amount of time a patient spent in a particular health state. Transitions between health states were linearly interpolated.

Additionally we will administer the EQ VAS. The EQ-VAS, a visual analog scale, generates a self-rating of health-related quality of life. The patient rates his/her health state by drawing a line from the box marked "Your health state today" to the appropriate point on the EQ-VAS on a scale of 0 to 100.

#### Hand grip strength

Hand grip strength (in kg) will be measured with a hydraulic hand dynamometer (Baseline, Fabrication Enterprises Inc., Elmsford, NY, USA). Respondents are asked to perform two maximum force trials with their non-dominant hand. The highest value will be used. Measured data will be compared to reference values by Mathiowetz. Data will be expressed as percentage of reference value [29].

